## Abstract

**Background:**

The prevalence of hand osteoarthritis (HOA) has been reported to be higher amongst women over 50 years old (66%) compared to men of the same age (34%). Although exercise therapy has been shown effective in reducing symptoms and disability associated with HOA, adherence to treatment programs remains low. The primary objective of this RCT is to examine the effectiveness of a 12-week knitting program for morning stiffness (primary outcome) and pain relief (secondary outcome) 2 h post-wakening in females (aged 50 to 85 years old) with mild to moderate hand osteoarthritis (HOA).

**Methods/design:**

A single-blind, two-arm randomized controlled trial (RCT) with a parallel group design will be used to reach this objective and compare results to a control group receiving an educational pamphlet on osteoarththritis (OA) designed by the Arthritis Society. The premise behind the knitting program is to use a meaningful occupation as the main component of an exercise program. The knitting program will include two components: 1) bi-weekly 20-min knitting sessions at a senior’s club and 2) 20-min home daily knitting sessions for the five remaining weekdays. Participants assigned to the control group will be encouraged to read the educational pamphlet and continue with usual routine. Pain, morning stiffness, hand function, self-efficacy and quality of life will be measured at baseline, six weeks, 12 weeks (end of program) with standardized tools. We hypothesize that participants in the knitting program will have significant improvements in all clinical outcomes compared to the control group.

A published case study as well as the preliminary results of a feasibility study as examined through a 6-week pre-post study (*n* = 5 women with HOA) involving 20-min daily knitting morning sessions led to this proposed randomized controlled trial research protocol. This article describes the intervention, the empirical evidence to support it.

**Discussion:**

This knitting RCT has the potential to enhance our understanding of the daily HOA symptoms control and exercise adherence, refine functional exercise recommendations in this prevalent disease, and reduce the burden of disability in older women.

**Trial Registration:**

(ACTRN12617000843358) registered on 7/06/2017.

## Background

Osteoarthritis affects a large proportion of the world population and hand osteoarthritis (HOA) represents the highest age-standardized total prevalence (43.3%) in terms of joint site compared to hip OA (23.9%) and knee OA (10.9%) [1]. A higher age-standardized total prevalence of HOA is observed amongst women over 50 years old (65.8%) compared to men of the same age (34.2%) [2]. The prevalence of HOA is expected to increase with the aging of the population [3]. HOA is recognized as a significant cause of disability resulting in activity and participation limitations as well as reduced quality of life (QoL) [4, 5] due to presence of pain, morning stiffness, tenderness and swelling of the fingers joints, diminished grip strength and psychological problems [2, 6].

Active hand exercises (i.e. strengthening exercises and yoga) have been shown to be an effective strategy to reduce morning stiffness [7, 8] and pain [9–11], increase range of motion [12, 13] grip and/or pinch strength [7–9, 11–16] improve hand functional status in HOA [8, 10] and reduce disease activity [7]. To our knowledge, no studies examined the effect of functional activities in the management of HOA. Several authors suggested that there is an urgent need for more trials of nonpharmacological and nonsurgical interventions for HOA [8, 17–20].

Isometric contractions (i.e. a type of muscle contraction involved knitting) have been shown effective to reduce pain perception, both in healthy individuals and in patients suffering from chronic pain [21, 22]. For healthy individuals, long duration activity (30 min) seems to be necessary to trigger exercise-induced hypoalgesia [22, 23]. For patients with chronic pain, meaningful change in pain is observed both for high and low intensity exercises protocols [21, 24, 25]. Psychosocial aspects can also contribute to the beneficial effects of exercise on pain [22, 26, 27].

According to the Canadian Model of Occupational Performance and Engagement (CMOP-E), [28] occupations bring meaning to life. Occupational therapy explores the therapeutic potential of occupations; it is believed that the power and the positive effects of occupations are greater when client can choose, control and get a sense of accomplishment through them. The movements typically incorporated in hand therapy for HOA (finger exercises [9] and muscle activation [22, 23] are also present in knitting. Knitting can be considered a purposeful and meaningful occupation. As such, knitting may be more appealing and meaningful for elderly women to participate in compared to regimented exercises programs. This study embeds the functional activity of knitting in an exercise program that may demonstrate greater adherence than regimented hand exercises [29]. Knitting also represents a promising activity for older individuals suffering from HOA pain via its potential effect on psychological and social factors (e.g. positive effect on mood and social isolation, particularly if knitting is done at a senior’s club). Indeed, it could be more appealing, motivating, enjoyable and rewarding to perform an activity that is highly appreciated [30] than a series of prescribed therapeutic exercise. To our knowledge, no studies have examined the effect of functional activities in the management of HOA.

In this research protocol, knitting is used in a larger context. It is prescribed and is structured in terms of frequency and duration, but not regarding intensity, style of knitting or needles holding (respect of personal fashion and willingness)) and is a replacement of a traditional prescribed exercise program during a therapy. A therapeutic aim would be to prevent morning stiffness as much as possible to maintain a regular level of daily activities. The proposed randomized controlled trial (RCT) will incorporate meaningful occupation (i.e. knitting) within a structured and supervised context.

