### Study design

The study is a single blind, two-arm RCT with a parallel group design to compare two study groups: 1) a knitting intervention (Group 1) and 2) a waiting list control group (Group 2). The intervention period will be 12 weeks plus a follow-up at 4 weeks post-intervention to measure the retention effect. Since this RCT involves a physical intervention (i.e. knitting program), the therapist, participants, and research coordinator administering the program will not be blinded. A blinded independent assessor will be trained to assess the participants though performance evaluation and self-reported questionnaires given at baseline, 3,6,9,12-week as well as at 4-week follow-up to reduce detection bias. With training and standard operating procedures, it is anticipated that any performance bias due to unblinding will be minimized. The study design flow chart is presented in Fig. 1. The study protocol is approved by the University of Ottawa Research Ethics Board (#H02–16-12).

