### Intervention

Participants in both groups will continue with their on-going medical care To measure the true effect of the knitting intervention, active hand exercises need to be avoided since they are proven effective for HOA [7, 9–16, 61]. This may not be possible thus all participants will complete a daily activity log.

Participants in **Group 1** will take part in a low-intensity knitting program, performed as a morning functional activity, which will comprise two components: 1) bi-weekly 20-min knitting sessions at a senior’s club and 2) 20-min home daily knitting sessions for the five remaining weekdays over 12 consecutive weeks (total of 90 sessions). The bi-weekly 20-min knitting session will take place, at **a Senior’s Club in metropolitan Ottawa,** on Tuesday and Thursday mornings with a group of regular members who knit wool blankets for sick children admitted CHEO, a regional Children’s Hospital. The blankets are composed of individual squares that are assembled together. Each wool square takes approximately 20 min for a beginner knitter. Each knitter will be encouraged to knit one wool square per day for a total of seven squares per week. To avoid excessive isometric strength and potential muscle fatigue with the use of small needles that require precise pinching, participants will use specific knitting needle and wool sizes (sizes #6 and #5 respectively according to the Standard Yarn Weight System (**http://www.craftyarncouncil.com/weight.html**). Study participants will learn how to knit with a qualified instructor from Senior’s Club during the knitting sessions which will also be supervised by a trained OT to ensure that the physiological and clinical characteristics of therapeutic exercise are being met. A knitting instructor will ensure that participants follow the prescribed program and if their individual logbooks, where they recorded their daily hand activities and morning stiffness and pain levels, are filled properly. In the event that a session is missed, participants in Group 1 will receive a telephone reminder from the research assistant to encourage them to attend the next session. At the end of 12 weeks, participants will be encouraged to continue on with the program if they gained an improvement of their condition.

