Potential information bias includes the imprecision of self-reporting outcomes [78]. The inclusion of performance-based physical function measures (e.g. Functional Index for Hand OA (FIHOA) [69] rather than solely measuring self-reported measures (e.g. AUSCAN function subscale) [62, 63] would help address these limitations. The primary and secondary outcomes, respectively morning stiffness and pain, are self-reported, but represent important unwanted symptoms that have functional consequences that affect the QOL of individuals with HOA. Objective measures of these particular symptoms are difficult to obtain. However, pain and morning intensity using a visual analogue scale is recognized as a gold standard, since the nature of pain is a subjective perception/experience. Unfortunately, no technology can measure this personnel sensation outcome [79]. In addition to self-reported VAS measurements of pain and morning stiffness intensity before and after knitting, the number of squares knitted will be recorded in logs books to capture the knitting intensity/quantity. Daily self-reported VAS measurements of pain and morning stiffness intensity before and after knitting are important to be recorded in the participant’s logbook, because these symptoms have a negative impact in their functional activities and QoL. Logbooks is a tool that can be useful to minimize potential recall biases. It might also be difficult to discriminate between pain from fingers versus from thumb for each hand assessment. This is why it important to take into consideration intensity, location, timing and duration of pain and joint stiffness [55] in the assessment in each finger affected by HOA.

This proposed RCT is necessary to address questions of clinical and scientific importance for rehabilitation specialists in improving the QoL of elderly women with HOA living in Canada. The results of this study will likely be generalizable to older women with mild to moderate HOA. If the results of this proposed RCT are positive, this accessible activity may be generalized to individual home-based knitting or group-based knitting in existing social clubs. The results of this RCT may give evidence to health professionals of an effective alternative physical activity to suggest for their patients with HOA.

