## Conclusion

This knitting RCT has substantial potential to enhance our understanding of this functional activity on the management of HOA, refine dosage and adherence recommendations in older women for this prevalent disease and to ultimately reduce the burden of disability in this aging population. This proposed RCT will contribute to the knowledge of the effect of knitting for individuals with HOA on self-reported and performance-based, HOA symptoms, level of QoL as well as fingers strength hand function and their self-efficacy and exercise adherence.

This proposed knitting RCT could also determine if this functional self-management activity has a daily and punctual effect on symptoms (i.e. HOA morning stiffness or pain) relief only (similarly to acetaminophen a pain reliever) or has also an effect on clinical and implementation outcomes,

This study could also make knitting the standard-of-community-based-care for older women with HOA. Moreover, other rehabilitation or functional interventions could be examined for older people with other chronic diseases.

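### The Conclusion's dosage, adherence and standard-of-care claims exceed what one knitting regimen against a waiting list can show, and adherence as defined cannot be compared between arms

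*Protocol article*

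**What the plan says.** **Design.** The Study design section names two groups: "1) a knitting intervention (Group 1) and 2) a waiting list control group (Group 2". The objectives and hypothesis at the end of the Background are framed against that waiting list. The Abstract describes the control differently, as an educational pamphlet with usual routine.

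**Hand exercise.** The Background lists morning stiffness among the symptoms that active hand exercise reduces. The Intervention section says that "active hand exercises need to be avoided since they are proven effective for HOA". It adds at once that avoidance may not be achievable, so all participants keep a daily log. People receiving rehabilitation treatment are excluded.

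**Rationale.** The Background says that knitting "is a replacement of a traditional prescribed exercise program during a therapy", and that an exercise program built on it "may demonstrate greater adherence than regimented hand exercises". The Strengths and limitations section says that positive results "may give evidence to health professionals of an effective alternative physical activity to suggest for their patients with HOA".

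**Conclusion.** The trial is said to have substantial potential to refine recommendations on dosage and on adherence. The section then states: "This study could also make knitting the standard-of-community-based-care for older women with HOA". The Abstract's discussion makes a similar claim about functional exercise recommendations.

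**Adherence.** The Implementation outcomes section defines it as knitting sessions attended or done at home, divided by the 84 prescribed. The Statistical analysis section lists it among the outcomes compared by two-way ANOVA with group (knitting or control) as the between factor.

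**The concern.** The document motivates knitting largely by contrast with prescribed hand exercise and ends by looking towards dosage advice and a standard of care. The trial contains no exercise arm and only one knitting schedule. A win over the waiting list would show that the supervised knitting program is better than the control condition. It would not show that knitting is as good as exercise, is better adhered to, or is given at a suitable dose. A reader who takes the Conclusion at face value could treat such a win as grounds for setting a community standard, although exercise, which the protocol regards as already proven, was never compared.

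Adherence raises a separate, more technical problem. It appears in a between-group analysis although its definition has meaning in one arm only. A significant group effect there would be an artefact of assignment, and it could be quoted as support for the adherence claim.

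**Working it through.** **1. The plan's own figure.** Inputs from the Sample size calculation section: effect size 0.8, power 80%, significance level 0.05 (taken as two-sided; the section does not say), 28 per group, 5% dropout, 30 recruited.

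- Normal approximation: n = 2(1.960 + 0.842)² / 0.8² = 24.5, so 25 per group.
- t-test version: 26 per group. The stated 28 is slightly conservative.
- Dropout: 28 / 0.95 = 29.5, so 30, as stated.
- Power at 28 per group: noncentrality 0.8 × √(28/2) = 2.99 with 54 degrees of freedom gives 83.6%. At 30 per group it is 86.1%.

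The sample size serves the stated question.

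**2. What that test can say about exercise.** Let knitting exceed the waiting list by 0.8 SD, as planned, and let exercise exceed it by E. No value of E is given, so assume 0.4 to 1.2 SD.

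| Assumed E | Knitting minus exercise | Chance of a significant knitting vs waiting-list result |
|---|---|---|
| 0.4 | 0.8 − 0.4 = +0.4 SD | 83.6% |
| 1.2 | 0.8 − 1.2 = −0.4 SD | 83.6% |

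E does not enter the contrast, so the last column cannot change. This holds for any trial without an exercise arm. It marks the limit of the inference and is not an error in the calculation.

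**3. Why adding an exercise arm is not the cheap answer.** The protocol states no non-inferiority margin, so the margins here are assumed. With one-sided alpha 0.025, power 80% and true difference zero, n per group = 2(1.960 + 0.842)² / margin². A margin of 0.5 SD needs 63, 0.4 SD needs 99, and 0.2 SD needs 393, all before dropout. With 28 per group, power would be about 46%, 32% and 11%.

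**4. Dosage.** One schedule is tested against none. No two knitting doses are randomised, so the randomised comparison yields no dose contrast.

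**5. Adherence.** For Group 1 the measure is sessions done / 84. Controls are prescribed no sessions and are barred from the club sessions until the study ends. Their value is therefore 0/0, which is undefined, or, if 84 is used as a fixed divisor, close to 0/84 = 0 by design. Either way, the group effect in the ANOVA reflects who was assigned to knit. The assessment schedule marks the enjoyment scale as Group 1 only but does not mark adherence that way.

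Group 1 adherence is also selected upward, because people unwilling or unable to adhere to the knitting program are excluded. It cannot fairly be set against exercise adherence reported elsewhere.

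**The case against.** The strongest reply is that the trial never sets out to compare knitting with exercise. The objectives and hypothesis are confined to the waiting list, no equivalence or non-inferiority test is planned, and the protocol reports no earlier study of functional activities in this disease. Testing first against no active program is then a reasonable step. All of this stands.

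Three stronger readings are tempting, and the document does not support them.

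- *The trial claims it will show that knitting can replace exercise.* The Background sentence comes straight after a description of how knitting is prescribed here, and it describes the role knitting takes in this protocol. The adherence sentence says only that it may be greater. In the Strengths and limitations section, "an effective alternative physical activity to suggest for their patients with HOA" follows a conditional and can mean one more option, which a win over a waiting list could support.
- *Controls are told not to exercise.* The avoidance statement sits in a paragraph about both groups, is hedged immediately, and quotes no instruction to controls. The Abstract has controls continue their usual routine.
- *The sample size is wrong or inadequate.* It reproduces within two participants per group and fits the waiting-list question.

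The reply does not cover the Conclusion. Tentative wording cannot supply a dose contrast or a comparator that the design lacks. Nor does the limitations section help: it discusses the waiting list only as a constraint on duration and never notes that a comparison with exercise is impossible.

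**Conclusion.** The concern holds in a limited form. The design, the objectives and the sample size are sound for the question of knitting against the control condition. The dosage, adherence and standard-of-care statements in the Conclusion go beyond that question. The trial gives no estimate of knitting relative to hand exercise, on symptoms or on adherence, because nobody is assigned to exercise.

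The between-group analysis of adherence has no valid interpretation under the protocol's own definition. The primary analysis is unaffected.

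The argument about comparator and dose needs no numerical assumption. The exercise effects of 0.4 and 1.2 SD and the non-inferiority margins are assumed for illustration. The 83.6% assumes a two-sided test and the planned effect of 0.8. The conclusion is the same whether the control is a waiting list or a pamphlet with usual routine, since neither is exercise, but the document has to settle which was used.

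**What to change.** - **Conclusion:** delete the claims about refining dosage and about a standard of community-based care. Limit the conclusion to the knitting program compared with the control condition actually used, and drop any suggestion that adherence advice will follow from a comparison. Bring the matching sentence in the Abstract's discussion into line.
- **Strengths and limitations:** state that no comparison with hand exercise is possible, on symptoms or on adherence.
- **Statistical analysis:** remove adherence from the between-group ANOVA and report it for Group 1 only, as an estimate with a confidence interval. Make the same edit where adherence is listed in the secondary objective, and mark it as Group 1 only in the assessment schedule. Hand physical activity level is logged in both arms and can stay as a between-group outcome.
- **Adherence denominator:** the Intervention section totals 90 sessions and the Implementation outcomes section uses 84. The two must be reconciled before the estimate is reported.
- **Control condition:** reconcile the Abstract (pamphlet and usual routine) with the Study design and Intervention sections (waiting list).

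No participants, arms or visits are added. The cost is a narrower, less favourable claim and one fewer between-group comparison.

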The proposed knitting program is based on: 1) evidence stemming from physiological studies [34–36]; 2) recommendations for individuals over 50 years old with OA [37] and specifically with HOA [12]; 3) evidence-based general exercise protocols for HOA [5, 38, 39] and OA of the thumb [40–42]; 4) current RCTs on therapeutic exercises for HOA [9, 14] and on the case study parameters described above [43]. In the proposed study, knitting will be a low-intensity hand exercise therapy comprising bilaterally dynamic and isometric movement of fingers, thumbs and wrists. Despite knitting being endorsed by The Arthritis Foundation [44] devoted to arthritis as a therapeutic activity for adults living with HOA, to our knowledge, no other comparative study studied its effectiveness on reducing symptoms related to HOA, potentially decreasing their impact in daily life and thus improving quality of life.

The primary objective of this RCT will be to examine the effectiveness of a 12-week knitting program for morning stiffness (primary outcome) and pain relief (secondary outcome) for participants in the knitting in Group 1 compared to participants in the control group assigned to a waiting list (Group 2) in older females (aged 50 to 85 years old) with mild to moderate osteoarthritis of the hands (HOA) after 2 h post-awakening. The secondary objective is to determine if older females with mild to moderate HOA using an adapted knitting program (Group 1) have improved hand and finger strength and physical function, self-efficacy, hand physical activity level and adherence, global patient improvement as well as quality of life (QoL) compared to a waiting list control group (Group 2) over 12 weeks of intervention and after a follow-up at 4 weeks post intervention. Our general hypothesis is that older females with mild to moderate HOA in the 12-week knitting group (Group 1) will have significant improvements in all daily clinical and implementation outcomes compared to the participants in the waiting list (Group 2) after 12 weeks of intervention.

